**Figure 1 F1:**
[figure not shown]
Study procedure and flow of participants through the trial.

### Randomisation and allocation

Participants are randomised 1:1 to either 1) the SmaRTWork intervention in addition to usual care or 2) usual care only using permuted blocks of random size. The randomisation is performed using a web-based solution (eForsk) provided by the research unit at St Olavs University Hospital, Norway. This unit is a third party and not otherwise involved in the conduct of the trial. To ensure allocation concealment, block sizes are not disclosed to study personnel, and the randomisation code is generated automatically by the software. Participants are informed about their group allocation via email from a project worker not involved in the analyses. Those randomised to the intervention group also receive a link to a webpage with instructions for downloading and using the app, including videos and answers to common technical questions. The app includes an onboarding procedure that explains its core functionality and how to use it.

### Intervention

#### Development of SmaRTWork

We used the intervention mapping framework^26^ to guide the development of the intervention. This approach ensures that existing evidence, theory, clinical expertise and user and stakeholder perspectives inform all developmental stages of the intervention. The project team involved in the development of the intervention included researchers with backgrounds in medicine (two specialists in physical medicine and rehabilitation and one in insurance medicine), physiotherapy, movement science, computer science, social anthropology, epidemiology, as well as a collaborator from Nav’s research and development department. The research group has experience from several previous trials involving sick-listed workers, and we used knowledge from interviews with sick-listed workers and various stakeholders (Nav caseworkers, clinicians, employers) in previous studies (eg,^27
28^). In addition, we reviewed the literature, performed new interviews with Nav case workers and included expert opinion from clinicians. In step 1 of the intervention mapping process, we developed a logic model of the problem based on the PRECEDE model (figure 2).^29^ The model was developed from right to left but is read from left to right.^26^ The main goal was identified as increasing sustainable return-to-work through strengthening perceived workability. We also identified subgoals: 1) increase self-efficacy for managing musculoskeletal pain and 2) reduce fear and worry about physical activity both in work settings and in everyday life. In step 2, we defined expected programme outcomes and formulated performance objectives for each of the outcomes, that is, a description of specific behaviours the target group must adapt to achieve the desired changes^26^ and steps for how the intervention could target each objective. As this is a self-management intervention, we focused on individual-level and modifiable determinants of return-to-work and MSD management (online supplemental table S1). The last task of step 2 was to create a matrix of change objectives by aligning performance objectives with individual-level determinants, knowledge, skills, self-efficacy and attitudes/beliefs/emotions (online supplemental table S2).

**Figure 2 F2:**
[figure not shown]
A logic model of the problem based on the PRECEDE model. Nav, Labor and Welfare Service; PRECEDE, Predisposing, Reinforcing, and Enabling Constructs in Educational Diagnosis and Evaluation.

During step 2, it became clear that our objectives aligned closely with the content of the selfBACK app, developed in a recent EU-funded project to support self-management of low back pain.^19
30^ We therefore decided to further develop the selfBACK app for this new target group, with a particular focus on updating and expanding the return-to-work-related educational content. In addition to adding new material, we also conducted interviews with patients (n=12) with MSDs taking part in a rehabilitation programme in secondary care to review and revise the existing content. Technically, the SmaRTWork platform was updated by reimplementing the decision-support backend from the original selfBACK system and modernising the mobile app codebase. The backend was rebuilt to support the SmaRTWork version of the intervention while preserving the core logic needed to deliver individualised self-management recommendations. In parallel, the mobile application was updated to address security vulnerabilities, improve compatibility with current software dependencies and ensure that the app could be maintained and deployed safely in the SmaRTWork study context.

Since the SmaRTWork app is based on the selfBACK app, the theories underpinning behaviour change and engagement remain the same and have been described previously.^31^ In short, the intervention builds on the Transtheoretical Domains Framework,^32^ which is an overall framework encompassing 33 behaviour change theories, and on Normalisation Process Theory,^33^ which helps explain how technology-based interventions are adopted, embedded and integrated into daily routines.^34^

#### The SmaRTWork intervention

Participants randomised to the intervention group will receive access to the SmaRTWork intervention in addition to usual care. The intervention is intended to supplement, not replace, follow-up by healthcare personnel. The intervention consists of an app and a Nav component that put participants in contact with their caseworker at Nav. All participants in the intervention group will get access to the app, while the Nav component will only be offered to those indicating its relevance in the baseline questionnaire.

The app provides individually tailored weekly self-management plans by matching the participant’s health information and sick leave status with tailored educational messages, physical activity advice and exercise recommendations via a decision support system. The system is a data-driven recommender system that uses the case-based reasoning methodology^35
36^ to capture and reuse information from successful participant cases in order to suggest the most suitable self-management plan for a participant (online supplemental figure S1). Case-based reasoning is a well-established methodology within artificial intelligence. Data sources for the case-based reasoning system include participant data collected through the baseline web-based questionnaire and weekly reports submitted by the participant in the SmaRTWork app (including pain, function, fear-avoidance, workability, sick leave status, sleep, self-efficacy, stress, health beliefs and barriers for physical activity). Only questions relevant for a given participant (ie, based on baseline information and progress) are included in the weekly report. This weekly information is used to revise the individually tailored self-management plan by matching the characteristics of the current participant case with existing successful participant cases in the SmaRTWork case-base. A full description of the design of the decision support system has been published elsewhere.^30
37^ All interactions between the participant and the SmaRTWork decision support system happen via the app. There is no interaction between the system and healthcare providers or Nav. The app will be available to the participants in the intervention group the entire duration of the study. Participants decide for themselves how long and how frequently they want to use the app. It is also possible to stop using the app for a period and resume use.

The weekly self-management plan is structured around three main content types: 1) physical activity level and goals (ie, number of steps), 2) strength and flexibility exercises and 3) educational material. Participants are asked to set a physical activity goal, and if they achieved last week’s goal, the app suggests a gradual increase in daily steps. Participants can view their daily step count in the app. The weekly individualised exercise programme includes a short video of each exercise and written instructions. The educational material consists of 21 main components (‘information about musculoskeletal pain’, ‘understanding the mind-body connection’, ‘self-management for musculoskeletal pain’, ‘thoughts, behaviour, attitude and feelings’, ‘fitting in self-management in a busy life’, ‘first aid pain flare-up’, ‘musculoskeletal pain and comorbidities’, ‘goal-setting and action planning’, ‘pacing and graded activity’, ‘problem solving’, ‘relaxation’, ‘sleep and musculoskeletal pain’, ‘social support’, ‘overcoming barriers for self-management of musculoskeletal pain’, ‘keeping active when sick-listed’, ‘staying in contact with the workplace’, ‘handling workplace conflicts’, ‘rights and duties while sick-listed’, ‘work-life interaction’, ‘return-to-work as a process and making a plan’ and ‘considering changing job’). Each day, the participants receive a short educational message (about 140 characters long) tailored to their profile, symptoms and progress. The message also includes a link to a longer, more explanatory text or tools that support self-management of MSDs and return-to-work due to MSDs, such as a goal-setting tool, mindfulness audio and sleep advice.

In addition, the app contains a toolbox and a statistics page for the three components. The toolbox includes a library of educational messages and exercises the participant has received in previous weekly plans, general information on managing MSDs, pain relief exercises that can be used if symptoms worsen and information on sleeping positions when in pain.

To be offered a new self-management plan for the coming week, participants must open the app at least once a week. The app sends push notifications to remind participants to use the app. The goal of the intervention is to help participants acquire the necessary knowledge and skills to self-manage their musculoskeletal complaints and empower them in their return-to-work process. As participants become more confident in their self-management abilities, they may reduce or discontinue app use. Therefore, discontinuation is not necessarily a sign of low compliance but may instead reflect improved self-management. Based on this, per protocol, analyses will not be performed, but we will report on app usage.

The Nav component of the intervention is offered to a subset of participants based on their baseline questionnaire response. There is usually no contact between the sick-listed person and their caseworker at Nav in the initial stage of a sick-leave period. The aim of this component is therefore to establish contact when it is relevant and desired by the sick-listed worker. The baseline questionnaire is designed to identify participants who may face challenges related to i) work accommodations, ii) workplace conflicts, iii) extensive caregiver responsibilities for children, family members or others, iv) financial difficulties or v) concerns about returning to their current workplace. If participants report one or more of these challenges, they are offered to discuss the issue with Nav directly. Participants in the intervention group who indicate that such contact would be useful are called by a research team member, who offers to forward this information to Nav. If the participant agrees, the information is forwarded, and the participant’s caseworker at Nav will reach out to them. Together, the participant and caseworker determine the appropriate measures, which are not restricted by the project.

#### Usual care

Participants randomised to the control group will receive usual care. This consists of sick leave follow-up as described under *Study context* and other recommendations made by the participant’s general practitioner and other clinicians they are seeing, for example, physiotherapists. There will be a considerable variation in these recommendations, as there is no defined treatment for this patient group. Clinical guidelines and recommendations for back, neck and widespread musculoskeletal pain endorse patient education, general physical activity and exercise.^5
38^ Therefore, recommendations by the general practitioner usually include self-management strategies, referrals to physiotherapy or other healthcare professionals or referral for specialist assessment at an outpatient clinic for physical medicine and rehabilitation. The study does not put any restrictions on what is offered as usual care.

### Outcomes

The primary outcome is time to sustainable return-to-work, defined as one consecutive month without receiving medical benefits, assessed over a 12-month period from randomisation using registry data. No individual adjudication will be performed, as the outcome status for each participant will be determined automatically based on an algorithm applied to the registry data. This outcome was selected because the aim of the trial is not only to achieve return-to-work but a sustained return-to-work. This is a widely used outcome in national and international research on return-to-work interventions^21
39
40^ and aligns with ongoing efforts to establish a core outcome set for work participation.^41^ If the intervention is effective, we will also assess long-term outcomes at 2 years and up to 10 years of follow-up. Registry data will be obtained from Nav, which include exact dates of sick leave spells and monthly information on long-term benefits (work assessment allowance and disability pension).

Secondary work participation outcomes include the number of sickness absence days during follow-up and the probability of working (ie, not receiving medical benefits) each month during the 12 months of follow-up, measured as repeated events, based on registry data from Nav. Additional secondary outcomes collected via questionnaires include: musculoskeletal health measured by the Musculoskeletal Health Questionnaire, health-related quality of life measured by the European Quality of Life-5 Dimension questionnaire,^42^ average pain last week measured by a numeric rating scale,^43^ confidence in ability to cope despite pain as assessed with the Pain Self-Efficacy Questionnaire,^44^ depressive symptoms measured by the two-item Patient Health Questionnaire-2,^45^ fear avoidance beliefs measured by the one-item Tampa Scale of Kinesiophobia,^46^ stress measured by the Perceived Stress Scale,^47^ illness perception measured by the Brief Illness Perception Questionnaire,^48^ symptoms of insomnia by items from the HUNT populations study,^49^ work ability measured by the single item from the Work Ability Index^50^ and the overall improvement assessed by the Global Perceived Effect scale.^51^

### Data collection methods and additional data

Questionnaire data are collected by web-based questionnaires at 3, 6 and 12 months of follow-up (online supplemental file 2). Table 1 shows the timeline for the enrolment, interventions and assessments. In addition to the aforementioned questionnaires, the baseline questionnaire includes items on socio-demographic variables: age, gender (man, woman, other gender identity with options non-binary, transgender, intergender, gender questioning, unsure and do not want to answer), height, weight, education (lower secondary school, upper secondary school, vocational school, university/college≤4 years and university/college>4 years), living situation (alone, partner, parents, other adults, young children, older children), work type and employment status, sick leave status, comorbidity (eg, heart disease, diabetes, depression), pain duration, use of pain medication and pain location. The latter is measured through a list with up to nine body parts, such as, neck, back, hips and knees.

**Table 1 T1:** Timeline for enrolment, interventions and assessments

	Enrolment	Allocation	Post-allocation			Tailoring*
Timepoint		Baseline	3 months	6 months	12 months	weekly
**ENROLMENT:**						
Eligibility screen	X					
Informed consent	X					
Allocation		X				
**INTERVENTION/** **COMPARATOR:**						
SmaRTWork						
Usual care						
**ASSESSMENTS:**						
Demographics†		X				
Work type and employment status		X				
Sick leave status		X	X	X	X	X
Factors contributing to sick leave‡		X				
Workability		X	X	X	X	X
Average pain past week		X	X	X	X	X
Worst pain past week		X	X	X	X	
Pain duration		X				
Pain locations		X				
Comorbidity		X				
Health-related quality of life (EQ-5D)		X	X	X	X	
Insomnia symptoms		X	X	X	X	X§
Fear avoidance		X	X	X	X	X§
Pain self-efficacy		X	X	X	X	X§
Brief illness perception		X	X	X	X	
Perceived stress		X	X	X	X	X§
Depressive symptoms		X	X	X	X	X§
Musculoskeletal health		X	X	X	X	
Global perceived effect			X	X	X	
Pain-related function						X
Barriers for self-management						X
Registry data¶						
Qualitative studies					X	

* Weekly responses reported by the participant in the SmaRTWork app. The responses are used to revise the individually tailored self-management plan. Only questions relevant for a given participant (ie, based on baseline information and progress) are included in the weekly reporting.

† Age, gender (man, woman, other gender identity with options non-binary, transgender, intergender, gender questioning, unsure and do not want to answer), height, weight, education (lower secondary school, upper secondary school, vocational school, university/college≤4 years and university/college>4 years), living situation (alone, partner, parents, other adults, young children, older children), work type and employment status.

‡ Challenges related to work accommodations, workplace conflicts, extensive caregiver responsibilities for children, family members or others, financial difficulties and concerns about returning to their current workplace.

§ For the tailoring, only a subset of the items in the questionnaire is used.

¶ Data on use of medical benefits (sick leave, work assessment allowance and disability benefits) and healthcare utilisation (primary and specialist healthcare).

EQ-5D, EuroQol-5 Dimension.

### Qualitative studies and process evaluation

Individual interviews will be conducted with the sick-listed individuals. The interviews will address their experiences with the SmaRTWork app, including their perspectives on individual tailoring, whether the app was user-friendly, their experiences implementing the suggested measures, how the app fit their needs and whether using the app affected their return-to-work process (interview guide in online supplemental file 4). Participants will receive an email invitation to participate in the interviews, including contact information for the researchers. The interviews will be analysed thematically^52^ using a theoretical framework inspired by actor-network theory.^53
54^ Interviews will be performed with participants in the pilot and in the RCT. For the latter group, interviews will be performed after 12 months to avoid influencing the intervention engagement or outcome reporting. We will also interview the case workers involved in delivering the Nav component. Although we aim to conduct focus group interviews with the case workers, we will convert to individual interviews if focus groups are not feasible to arrange (eg, due to participants’ travel time). In addition to the caseworkers’ own experiences, we will use vignettes (ie, anonymised cases) as a background for conversation in these interviews.

Through a process evaluation, facilitators and barriers to implementation will be investigated and described using the Reach, Effectiveness, Adoption, Implementation and Maintenance framework and the Practical Implementation Sustainability Model framework.^55
56^ We will use a mixed-methods design including both quantitative and qualitative methods. Specifically, we will combine quantitative data from the decision support system (eg, app usage, intervention engagement) with data from interviews with the sick-listed workers and case workers at Nav. The findings will contribute to understanding the effect, or lack thereof, of the intervention investigated in the RCT.

### Health economic evaluation

We will perform an economic evaluation, including a cost-effectiveness, a cost-utility and a cost-benefit analysis from both a healthcare and societal perspective. To enable the estimation of individuals’ healthcare costs, information on individuals’ healthcare utilisation will be retrieved from national registries, including the Norwegian Patient Registry and the Municipal Care Registry. Productivity loss due to sick leave will be calculated by multiplying the number of sickness absence days by the average wage in Norway retrieved from Statistics Norway. For the cost-utility analyses, the outcome will be quality-adjusted life years. For the cost-effectiveness analyses, the outcome will be sickness absence days, excluding productivity costs to avoid double counting. Cost-benefit analyses will compare costs and benefits between the intervention and control groups, calculating a net societal benefit. The health economic evaluation will be led by a health economist.

### Sample size

Sample size calculations based on the results of previous return-to-work interventions^57^ indicate that 149 participants are needed in each group (total 298). The calculation is based on a comparison of return-to-work using survival analysis with a log-rank test with a HR of 0.70 (survival probabilities (ie, no return-to-work) 0.1 and 0.2, alpha 0.05, beta 0.20). There will be no loss to follow-up due to the use of registry data for the primary outcome.

A detailed statistical analysis plan will be developed and uploaded to ClinicalTrials.gov before the randomisation code is unblinded. Time to sustainable return-to-work will be described by cumulative probability curves, and group differences will be assessed by HRs from Cox regression. Absolute and relative differences in the 1-year probability of sustainable return-to-work will be estimated from logistic regression, whereas differences in the probability of working each month during follow-up will be estimated using Poisson regression within a generalised estimating equation model. Differences in the number of sickness absence days at specific follow-up times (3, 6, 9 and 12 months) will be estimated using Poisson regression. Mean group differences in continuous secondary outcomes will be analysed using linear mixed models. The precisions of all estimated effects will be assessed by a 95% CI. All analyses will be performed by the intention-to-treat principle. The statistical model assumptions will be evaluated for all analyses, and if these are violated, alternative modelling approaches will be considered. All analyses will be adjusted for factors that are considered predictors of the outcomes under study (eg, education level) to improve precision. The details will be prespecified in the statistical analysis plan.

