### Blinding

Due to the nature of the intervention, the participants cannot be blinded to group allocation. The researchers performing analyses and interpretation of the results will be blinded to group allocation. Once the last participant reaches the 12-month follow-up, the data will be extracted from the database for statistical analyses. All personal information that may identify the participants or group allocation will be removed before the blinded analyses, and a blinded interpretation of the main result will be shared within the research group, agreed on and uploaded on ClinicalTrials.gov before group allocation is revealed. The randomisation code (identifying the groups) will be kept in the web solution used for allocation and only available for those performing the allocation.

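### The only stated deadline for the statistical analysis plan falls after the masked group comparison, so the text does not exclude fixing covariates and fallback models once its p-value has been seen

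*Protocol article*

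**What the plan says.** In the analysis paragraph under Sample size, the protocol article gives one milestone for the statistical analysis plan (SAP): "A detailed statistical analysis plan will be developed and uploaded to ClinicalTrials.gov before the randomisation code is unblinded". The same paragraph leaves two choices to that plan. On covariates: "All analyses will be adjusted for factors that are considered predictors of the outcomes under study (eg, education level) to improve precision". On model failure: "if these are violated, alternative modelling approaches will be considered". It closes with: "The details will be prespecified in the statistical analysis plan".

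The Blinding section sets the order of events at the end of the trial. First, "Once the last participant reaches the 12-month follow-up, the data will be extracted from the database for statistical analyses". Identifying information is then removed and the blinded analyses are done. Next, "a blinded interpretation of the main result will be shared within the research group, agreed on and uploaded on ClinicalTrials.gov". Allocation is revealed only after that. This section also says what the code is and who holds it: "The randomisation code (identifying the groups) will be kept in the web solution used for allocation and only available for those performing the allocation".

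**The concern.** A deadline for a SAP is useful if it falls before anyone can see how the groups compare under different analyses. The deadline stated here is the unmasking of the groups, which the Blinding section puts last. Between data extraction and that point, the team will have run the group comparison with masked labels and agreed in writing what the main result means.

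Masking stops an analyst from favouring a named arm. It does not stop anyone from preferring an analysis that gives a clear difference over one that does not. Every analysis is to be adjusted, so the primary Cox estimate depends on a covariate list that the article leaves open apart from one example. At stake is the nominal 5% error rate of the primary test, and the readers' ability to verify that the analysis was chosen before the comparison was seen.

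**Working it through.** **1. Order of events.** Setting the two sections side by side:

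1. The last participant reaches 12 months (Blinding).
2. Data are extracted for analysis (Blinding).
3. Blinded analyses are run (Blinding).
4. The blinded interpretation of the main result is agreed and posted (Blinding).
5. Allocation is revealed (Blinding). This is the SAP deadline (Sample size).

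The Blinding section describes the randomisation code as what identifies the groups, so unblinding the code and revealing allocation are the same event. A SAP uploaded between steps 4 and 5 would comply. The article names no earlier milestone. It does not describe the masked labels, but a blinded interpretation of the main result requires a comparison of two masked groups.

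**2. What masking hides.** Let the log hazard ratio for group A versus B be b, with standard error s. Then z = b/s and p = 2Φ(−|z|). Swapping the labels changes b to −b and z to −z. The p-value is unchanged, and so is the width of the 95% CI on the log scale, 2 × 1.96 × s. Masking hides only the direction.

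**3. What is fixed and what is open.** Fixed in the article: the outcome and its one-month definition, the 12-month horizon, automatic ascertainment from registry data, Cox regression for the primary comparison, the model families for the other outcomes, 95% CIs and intention to treat. Open: the covariates and their coding, and the model to use if assumptions fail.

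**4. The plan's own sample size.** Inputs from Sample size: HR 0.70, probabilities of no return to work 0.1 and 0.2, alpha 0.05 (taken as two-sided), power 0.80. By Freedman's formula:

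- events = (1.960 + 0.842)² × [(1 + 0.70)/(1 − 0.70)]² = 7.849 × 32.11 = 252.04, rounded up to 253;
- mean event probability = 1 − (0.1 + 0.2)/2 = 0.85;
- N = 253/0.85 = 297.6, rounded up to 298, or 149 per arm.

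This reproduces the stated figure. The SAP's date does not enter the formula, so moving it changes neither N nor alpha.

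**5. Illustration of what selection could do.** The number and strength of the covariates are assumptions, not taken from the article. Each simulated trial has 298 participants, 1:1 allocation and no true effect. The Cox runs have 85% events. The third column takes the smallest two-sided p-value over the allowed covariate sets.

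| Model and assumed covariates | Sets searched | Type I error, smallest p | Type I error, set fixed in advance |
|---|---|---|---|
| Linear, five covariates, R² = 0.20 (4000 runs) | all 32 | 10.8% | 4.7% (unadjusted) |
| As above, one covariate always included | 16 | 9.4% | not reported |
| Cox, four covariates, log-HR 0.2 per SD (1500 runs) | all 16 | 10.5% (Monte Carlo SE 0.8 points) | 4.8% (all four) |
| Cox, four covariates, log-HR 0.4 per SD (1500 runs) | all 16 | 17.5% (SE 1.0 point) | 6.0% (all four) |
| Cox, one forced and four optional, log-HR 0.2 per SD (1000 runs) | 16 | 9.6% | 4.3% (all five) |
| Cox, one forced and four optional, log-HR 0.3 per SD (1000 runs) | 16 | 14.3% | 5.7% (all five) |

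The rows that search all sets include the unadjusted model, which the article's commitment to adjust every analysis rules out. The rows with one covariate always included are closer to the plan. In the linear set-up, false positives favouring one given arm were about 5.4%, against a nominal 2.5%.

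**The case against.** The strongest reply is that the paragraph promises prespecified details. Details chosen after seeing the comparison would not be prespecified, so the two sentences together can be read as a commitment plus an outer limit for posting. This stands as evidence of intent, and it rules out a tempting stronger reading: that the SAP will be written late, or that the trial plans to choose its analysis from the results. The article says neither. But the only date attached to the commitment does not enforce it.

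Second, neither the SAP nor the full protocol is shown, and either may carry an earlier date. That is true. The point, however, concerns a deadline that this article states, not content that it leaves out.

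Third, little is left open. Covariates must be predictors of the outcome, and fallback models come in only if assumptions fail. Both restrictions narrow the choice. Neither names the covariates or the fallback, and judging whether an assumption has failed depends on the data.

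Fourth, a reader might infer that staff who know the allocation could steer the analysis. The documents do not support this. The worker who tells participants their group takes no part in the analyses, and those who analyse and interpret are blinded. Posting a blinded interpretation also guards against steering towards benefit. It protects the interpretation, however, and not the choice of model.

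Fifth, the simulated error rates rest on assumptions and on deliberate selection of the smallest p-value. This stands in full.

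**Conclusion.** The concern holds as a badly placed deadline. The article permits the adjustment covariates and the fallback models to be settled after the masked comparison and its two-sided p-value are known, and masking of the labels does not prevent that. The conclusion rests on the order of events in the two sections and needs no simulation.

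Its size cannot be derived from the article. Under deliberate selection, type I error was about 9% to 11% in the linear set-up and up to about 17% with strong covariates in a Cox model, against 5% nominal. A reader might take one of these figures as the trial's true error rate or as a ceiling. It is neither. It varies with the assumed covariates, choice among fallback models is not included, and nothing suggests that such selection is intended. This is a real weakness in protecting the primary test that is easily closed. It is not a fatal flaw, and the sample size is not in dispute.

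**What to change.** Replace the deadline under Sample size, and repeat it under Blinding, with wording such as: *The statistical analysis plan, including the list and coding of adjustment covariates and the fallback analysis if proportional hazards does not hold, will be finalised and uploaded to ClinicalTrials.gov before any analysis by (masked) group.*

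The simplest milestone to verify is the extraction of data for statistical analysis, because it is dated and comes before every group comparison. Locking the plan that early is convenient but not essential: pooled data without arm labels do not reveal the comparison, so finalising before the first analysis by masked group is enough.

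The blinded interpretation step stays as written. N remains 149 per arm and alpha 0.05. The only cost is an earlier date for a document that must be written anyway. Recruitment is expected to begin in autumn 2026 and extraction follows the last 12-month follow-up, so there is ample time.
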